rare instances, heart attack, stroke, and death. Cardiovascular events are assessed using standard protocol measures including ECGs. When a cardiovascular event has occurred, the study physician decides whether it is permissible for the participant to continue interventions. If the SPRINTT interventions are discontinued for safety reasons, they may be resumed after consultation with the participant's primary care physician.

Serious fall injuries and fractures are assessed using standard protocol measures, including radiographs and hospital records. When a serious fall injury or fracture occurs, a study physician decides whether it is permissible for the participant to continue interventions. If the SPRINTT interventions are discontinued for safety reasons, they may be resumed after consultation with the participant's primary care physician.

In the SPRINTT safety monitoring system, participants who report adverse events to any staff person at any time are referred to unblinded medical staff responsible for identifying, recording, and managing these events. Safety-related events are reported in a timely fashion as required by the DSMB and the Ethics Committee responsible for the study. Interventionists and other staff reporting or managing adverse events for safety purposes do not at any time communicate information regarding these events to study assessment personnel.

SPRINTT maintains an event outcome record that is completely separate and distinct from the safety monitoring system for the intervention group. This is necessary because many of the SPRINTT staff members are not masked to intervention assignment, and it is critical that the identification and reporting of serious adverse events for safety reasons not bias the study's collection of outcome data. Thus, for outcome purposes, all SPRINTT participants are systematically queried at clinic visits or phone calls according to the protocol to capture outcome data on study outcomes, medical events, or adverse experiences. This separate outcome record contains solely those adverse events that are reported through these interviews conducted by designated outcome assessment staff masked to intervention assignment.

All serious adverse events and deaths shall be reported within 48 hours to DSMB and to the Management Board. All Serious Adverse Events shall be reported in a summary format by the blinded treatment arm (A and B) to the DSMB and Management Board monthly.

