### 1.3 DETERMINATION OF SAMPLE SIZE

The sample size calculation was based on the LIFE-M study database ([1](#), [2](#)). Specifically, survival analyses were run according to different levels of Short Physical Performance Battery (SPPB) score (lower than 8, versus 8 and 9). The outcome considered was major mobility disability (i.e. inability to complete the 400-m walk test). The effect of PA on major mobility disability was negligible in participants with a baseline SPPB score  $\geq 8$  (hazard ratio=0.94; 95% confidence interval [CI]: 0.72-1.23;  $p=0.65$ ). Conversely, the hazard ratio was statistically significant in participants with a baseline SPPB score lower than 8 (hazard ratio=0.75; 95%CI: 0.59-0.94;  $p=0.012$ ).

- A sample of 1,200 older persons with SPPB score  $< 8$  enrolled over 12 months is estimated to provide 85% power (434 events) to detect a 25% reduction in the hazard of major mobility disability over a maximum of 36 months of follow-up, considering an exponential dropout rate of 25% over 2 years and a log rank test with a 5% two-sided alpha level. An interim blinded sample size reassessment after 11 months from the beginning of recruitment allows taking immediate actions to preserve the study power in case the efficiency of enrolment or the number of observed events is not coherent with the original assumptions.
- In addition to not restrict the enrolment to older people with SPPB score lower than 8 that would jeopardize the aim of project to comprehensively characterize the PF&S condition and to not decrease the study power hence, the probability of success of the trial, it was decided to include in the study a convenience sample of 300 older adults with baseline SPPB score 8 or 9. An ad hoc hierarchical testing procedure has been formulated to control type I error: first, we will compare the effects of the

interventions in participants with SPPB score lower than 8 and, only in case of significant result (i.e., two sided  $p < 5\%$ ), the comparison will be extended to the whole study population

- At the first blinded sample size reassessment (may 2017) it was decided to increase the accrual period by 6 months, but maintaining a maximum of 36 months of follow-up period
- The last participant was randomized on November 15th 2017 (1205 in SPPB<8 stratum, 314 in SPPB 8-9 stratum)

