#### 1.4 STUDY PLAN

Approximately 1500 participants will be randomized in a ratio 1:1 to the following two treatment groups:

- HALE programme (n = 750 ; approximately n=600 with SPPB<8 and n=150 with SPPB≥8)
- MCI programme (n = 750 ; approximately n=600 with SPPB<8 and n=150 with SPPB≥8))

In the MCI intervention group, the PA component is designed to be performed both at the center and at home. Participants will train at the center twice a week under direct supervision of instructors. The PA schedule below shows the expectation in term of center-based sessions and home-based exercises.

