#### **Adjudication of primary endpoint**

All 400-meter walk tests not performed (including missing tests due to visits performed by phone or proxy) will be adjudicated. A pre-defined algorithm will be applied to automatically adjudicate the missing tests (i.e. disability ascertained or no disability). Following this automatic adjudication, all remaining missing tests will be then evaluated by an adjudication committee.

The algorithm was built by identifying all the information recorded in the eCRF that was related to the participants' walking ability. Once selected, all this information (e.g. answers to questionnaires, results from the gait speed test, etc.) was then included in a logistic regression model run on all available 400-meter walk tests in order to determine which information was most predictive of the disability status (i.e. success or failure).

To adopt a conservative approach, the selected information was then fine-tuned to limit the number of tests wrongly classified as no disability to 5%. The number of tests wrongly classified as disability reaches 25%.

The resulting algorithm, based on result from the Gait speed test and some answers obtained from the ADL Proxy and Assistive Device questionnaires, is as follows:

1. "Disability ascertained" if:

- Gait speed test performed in 0.4 m/s or less **OR** participants not able to walk the 4 meters **OR** had to use an aid other than a cane to walk
- **OR** participants answer "Yes" to at least one of the following questions:
  - *"When the subject walks outside his/her home, does he/she usually require a walker?"*
  - *"When the subject walks outside his/her home, does he/she usually require a tripod or a quad cane?"*
  - *"When the subject walks inside his/her home, does he/she usually require a walker?"*
  - *"When the subject walks inside his/her home, does he/she usually require a tripod or a quad cane?"*

- **OR** participants answers “*Unable to do*” or “*A lot of difficulty*” to at least one of the following questions:
    - “*Walking for 400 metres, which is a little shorter than half a kilometre?*”
    - “*Walking for more than one kilometre because of your health?*”
  - **OR** participants answers “*Unable to do*” or “*A lot of difficulty*” or “*Some difficulty*” to the question “*Walking 100 metres because of your health?*”
2. “No disability” if:

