- Gait speed test performed in more than 0.67 m/s (less than 6 sec to walk 4 meters) without an aid other than a cane **OR** Lawton ADL score equal to 8
  - **AND** participants answer “*No difficulty*” to the 2 following questions
    - “*Walking for 400 metres, which is a little shorter than half a kilometre?*”
    - “*Walking 100 metres because of your health?*”
  - **AND** participants answer “*No difficulty*” or “*A little difficulty*” or “*Some difficulty*” to the question “*Walking for more than one kilometre because of your health?*”

Then, the adjudication committee will assess remaining missing 400-m walk tests using all information in the following available eCRF modules:

- 400-meter walk test
- Assistive device questionnaire
- PAT-D
- ADL Proxy
- Outcome events
- Adverse events

The 3 possible assessments by the adjudication committee are “Disability ascertained”, “No disability” or “Disability not conclusive” (i.e. when the outcome could not be adjudicated due to the lack of available information)

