### **Derivation of primary endpoint**

Disability will be considered ascertained:

- at the date of the 400-meter walk test, if participants fail to walk 400 meters within 15 minutes, or need an assistive device
- or at the date of the visit (or date of the 400-meter walk test if available) when the visit is performed but the participant did not perform the 400-meter walk test and the adjudication (automatic or from the committee) does not classified the event as no disability (i.e. ascertained or not conclusive) if any

- or at the date of death if the participants died during the study

Participants who have not met this disability criterion at the end of their study participation (including withdrawals) will be considered as right-censored observations. The censoring time will be calculated as the date of their last successful completed 400-meter walk test (including assessment of “no disability” by the automatic adjudication or the adjudication committee) minus the date of randomization visit V1-T0 (or date of randomization if V1 is missing) + 1 day.

**Particular cases:** In the case where more than 9 months are observed between two consecutive visits or between the last available visit and the death:

- If the disability criterion is not met at the 2nd consecutive visit, then participants will be censored at the date of their first consecutive visit. In the case where the first of the two consecutive visits is the randomization visit, then the censoring time will be equal to 1.
- If the disability criterion is observed at the 2nd visit of the two consecutive visits, or the participant died more than 9 month after the last available visit, then the disability will be considered ascertained at the date of the first consecutive visit or at the date of the last available visit before to die, plus 183 days (i.e., 6 months). In the case where the first of the two consecutive visits (or the last available visit before to die) is the randomization visit, then the disability will be considered ascertained at the date of randomization visit V1-T0 (or date of randomization if V1 is missing) + 183 days.

If no post-baseline visit is done, then participants will be censored at the date of randomization visit V1-T0 (or date of randomization if V1 is missing).

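### A completed visit with no walk test and a not-conclusive adjudication is scored as a primary event, no planned analysis tests that rule, and the committee that applies it is not stated to be masked

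*Combined protocol and SAP*

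**What the plan says.** SAP 2.1.3.1 sends every 400-metre walk that was not performed to adjudication, including those missed because the visit was by phone or proxy. An algorithm runs first. Built on walks that were done, it was tuned to hold false no-disability calls to 5%, and the SAP then states: "The number of tests wrongly classified as disability reaches 25" per cent. What the algorithm leaves open goes to a committee: "Then, the adjudication committee will assess remaining missing 400-m walk tests using all information in the following available eCRF modules". The last of the six modules listed is Adverse events. The committee may answer disability, no disability, or not conclusive, the last being used "when the outcome could not be adjudicated due to the lack of available information".

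The derivation section then makes a visit held without a walk test an event when the adjudication "does not classified the event as no disability (i.e. ascertained or not conclusive) if any". Participants who withdraw without an event are censored at their last passed or no-disability assessment, and those with no post-baseline visit at randomisation.

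Protocol 10.2.1 contains no such event rule. It censors participants without disability at their last primary outcome evaluation. SAP 1.6, which should list statistical changes, reads as not applicable. The only supportive analysis of the endpoint definition (SAP 2.4.4.1) takes deaths out of the event.

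On masking, protocol 7.4.3.3 blinds the assessment team. Protocol 11.9 sends adverse events to unblinded medical staff, keeps a separate outcome record, and says that staff handling events for safety purposes "do not at any time communicate information regarding these events to study assessment personnel". Neither document says whether the adjudication committee is masked.

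**The concern.** A not-conclusive result is missing data. Scoring it as an event makes the confirmatory endpoint depend partly on how often each arm has visits held without a walk and with a thin file. Equal rates cannot be presumed, because contact differs greatly: MCI trains at the centre twice a week (protocol 6.2.1.2), while HALE meets twice a month with attendance required once (6.3.1). Automatic clearance is also hard to obtain remotely. It requires no reported difficulty over 400 m and over 100 m, together with either a measured gait speed above 0.67 m/s or a Lawton score of 8, and gait speed cannot be measured by phone.

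The second strand is masking. The adverse-event categories in SAP 2.1.4.1 include falls during activity recommended by the study, and chest pain or dyspnoea that persists after exercise stops. Such entries can suggest the MCI arm to an adjudicator who decides whether to grant a no-disability result.

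At stake is whether a significant or a null primary result can be attributed to walking ability rather than to the pattern of untested visits. As planned, no output would show which.

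**Working it through.** **1. The plan's own figure.** SAP 1.3 specifies a "log rank test with a 5% two-sided alpha level" and says that the sample "is estimated to provide 85% power (434 events) to detect a 25% reduction in the hazard of major mobility disability". With 1:1 allocation, Schoenfeld's formula gives D = 4(1.960 + 1.036)² / (ln 0.75)² = 35.91 / 0.0828 = 434. The figure reproduces, and power at 434 events is 85.0%.

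**2. How large an imbalance matters.** With no true effect and 434 events in total, the between-arm difference in events has a standard deviation of about √434 = 20.8. Significance therefore needs a difference of 1.96 × 20.8 ≈ 41 events, or 6.8% of 600 per arm.

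**3. Simple model.** All rates here are assumptions. Let the disability hazard be 0.19 a year in both arms, and add not-conclusive events at rate a in MCI and b in HALE. Then HR = (0.19 + a)/(0.19 + b), z = ln(HR) × √434 / 2, and P(false benefit) = Φ(−1.96 − z).

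- a = 0.015, b = 0.03: HR = 0.205/0.220 = 0.932; z = −0.0706 × 10.416 = −0.736; P = Φ(−1.224) = 11.0%.
- a = 0.02, b = 0.04: HR = 0.210/0.230 = 0.913; z = −0.948; P = Φ(−1.012) = 15.6%.
- a = 0.03, b = 0.015: HR = 1.073, with the same 11.0% chance of a false result, now against MCI.

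The nominal chance in each direction is 2.5%. With the accrual, follow-up and dropout in step 4, the first two cases yield about 420 and 432 counted events, so 0.19 is compatible with the plan. They need only about 2.5% v 4.9%, or 3.3% v 6.5%, of participants to have a not-conclusive visit as first event. At a disability hazard of 0.22 a year the 11.0% and 15.6% become 9% and 13%.

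**4. Model with the plan's design features.** Inputs: 600 per arm, 12-month uniform accrual, 3-year maximum and 25% exponential dropout over two years (dropout hazard −ln(0.75)/2 = 0.144 a year). The common hazard that yields 434 events under no effect is 0.221 a year. Under HR 0.75, the control hazard that yields 434 is 0.254. Not-conclusive first events are added as the stated share of each arm.

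| True HR | Share MCI / HALE | Apparent HR | Chance of p<0.05 |
|---|---|---|---|
| 1.00 | 0 / 0 | 1.00 | 5.0% |
| 1.00 | 5% / 5% | 1.00 | 5.0% |
| 1.00 | 2% / 4% | 0.95 | 8.8% |
| 1.00 | 5% / 10% | 0.88 | 29.2%, nearly all for MCI |
| 1.00 | 10% / 5% | 1.13 | 29.2%, nearly all for HALE |
| 0.75 | 0 / 0 | 0.75 | 85% |
| 0.75 | 5% / 5% | 0.77 | 81% |
| 0.75 | 10% / 10% | 0.79 | 78% |
| 0.75 | 3% / 5% | 0.73 | 93% |
| 0.75 | 10% / 5% | 0.89 | 28% |

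Equal shares leave the type I error at 5% and dilute a real effect. Unequal shares bias the result in whichever direction the imbalance runs.

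**5. Dilution with the right comparator.** If a fraction q of 434 counted events is not real and is spread equally, the HR is roughly 0.75(1 − q) + q. For q = 10% and 20% that is 0.775 and 0.80, with power 76% and 64%. Removing those events leaves 434 × 0.9 ≈ 391 and 434 × 0.8 ≈ 347, with power at HR 0.75 of about 81% and 76%. The cost is therefore 76% against 81%, or 64% against 76%; setting either against 85% overstates it. These fractions would also include the algorithm's false positives, which changing the not-conclusive rule does not remove.

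**The case against.** Several stronger readings are tempting, and the documents do not support them.

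- *People who do not turn up become events.* They do not. The rule needs a visit; withdrawals and participants never seen again are censored. Exposure is limited to visits held without a walk that neither the algorithm nor the committee resolves.
- *The rule favours MCI.* The direction is not established. Since an event needs a contact, the arm with better retained contact could collect more not-conclusive events.
- *The SAP calls this rule conservative.* It uses that word only for the tuning of the algorithm. Leaning toward disability is not conservative for a comparison between arms, but the SAP makes no such claim for not-conclusive results.
- *The committee is unmasked and the protocol's separation is breached.* The documents are silent. Protocol 8.6 describes a blind data review with unblinding only after lock, and 11.9 protects assessment personnel, who may or may not include adjudicators. HALE also has instructor-led stretching, and both arms walk 400 m under supervision, so the items suggest MCI without proving it. Disability and not conclusive lead to the same outcome, so knowledge of the arm could act only through granting or withholding no disability.

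There is also partial mitigation. Persistent mobility disability cannot follow from one untested visit alone; it needs a second consecutive failure or adjudicated disability, or a death. Reasons for censoring are tabulated by arm. But the secondary endpoints are exploratory, and neither item isolates the rule.

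The best argument for the present rule stands: a frail person who attends but does not walk is probably not missing at random, so censoring at the last pass has its own bias. That is a reason to keep the rule as primary if the sponsor wishes, but it does not justify leaving it untested.

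**Conclusion.** The text is clear: lack of information at a completed visit counts as a primary event, the rule is not in protocol 10.2.1, SAP 1.6 does not declare it, and no planned analysis would reveal its influence. Equal not-conclusive rates dilute the hazard ratio; unequal rates bias it either way. On the assumed rates of 1.5% v 3% a year, the chance of a false benefit rises from 2.5% to 11%; the mirror image under a true effect would hide benefit. These sizes rest on invented rates, constant hazards and a normal approximation, and they show sensitivity only. The documents do not show that rates differ or in which direction.

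On masking, the supportable conclusion is a gap: the committee receives a module that can hint at allocation, and its masking is not stated. Actual unmasking is not documented.

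**What to change.** The present rule may remain primary. Before database lock, add to the SAP:

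1. A sensitivity analysis in which not-conclusive results are not events, with censoring at the last passed or no-disability assessment. If that censoring is non-informative, the null case returns to HR 1.00 and a 5% type I error.
2. A sensitivity analysis using only 400-metre walks actually performed.
3. Ideally, a tipping-point or multiple-imputation analysis by arm. Imputation needs care, since these cases are defined by sparse predictors.
4. A table of events by source (failed test, algorithm, committee, not conclusive, death) and arm.
5. A statement that the committee is masked, with supervised-activity and exercise-linked fields removed from its file. Keep the rest of the Adverse events module: fractures, hospitalisations and disability reports help resolve cases, and dropping them could create more not-conclusive results.
6. An entry in SAP 1.6 recording the rule as a change from protocol 10.2.1.

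The cost is SAP text, a few extra runs, and slightly less information for the committee. No new data are needed. If lock has passed, the runs and the table are still worth reporting, labelled post hoc.

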### 10.2.1. Primary efficacy endpoint

The primary comparison of intervention groups with respect to the distribution of time until the first post-randomisation occurrence of the primary outcome will be based on log-rank stratified by study site and gender. The primary comparison will be conducted only in study participants with baseline SPPB  $< 8$ . If this primary analysis is statistically significant ( $p < 0.05$ ), the comparison will be extended to include the remaining 300 participants with baseline SPPB 8-9. An additional binary indicator variable will be introduced denoting a baseline SPPB score  $< 8$  or  $\geq 8$  and its interaction with the intervention group. Hazard ratio and confidence interval will be computed for the whole population only if this interaction term can be ignored (i.e., if it is not statistically significant). The hazard ratio between intervention groups and the corresponding confidence interval will be computed using a Cox proportional hazard model with site and gender as co-variables for comparison in subjects with a SPPB score  $< 8$  and by adding

the SPPB score  $\geq 8$  flag and corresponding interaction term as co-variables for the comparison in the whole study population.

The time to event is defined as the time from randomisation to the date of first occurrence of disability. Participants who do not meet this criterion will be censored at the time of their last primary outcome evaluation. In secondary analyses, in order to take into account additional covariates, we will use a Cox proportional hazards model if the underlying assumptions appear warranted. The proportional hazards assumption will be verified by testing the treatment-by-time interaction in the Cox model.

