## 1.6 STATISTICAL MODIFICATIONS MADE IN THE STATISTICAL ANALYSIS PLAN

Not applicable

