### 2.1.3.1 Primary efficacy endpoint(s)

The primary endpoint is the time (in days) from randomization to the date of first occurrence of major mobility disability assessed by the inability to complete the 400-meter walk test within 15 minutes, without sitting, help from another person or use of a walker.

This time is calculated as date of event minus date of randomization visit V1-T0 (or date of randomization if V1 is missing) + 1 day.

The 400-meter walk test is assessed at Month 3 then every 6 months after the randomization visit.

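### The SAP's primary endpoint is an undeclared composite of mobility disability or death, while its name, objective and power statement still describe disability alone

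*Combined protocol and SAP*

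**What the plan says.** **Protocol.** Section 10.1 defines the primary endpoint as time to first inability to complete the 400-m walk in under 15 minutes. Section 10.2.1 adds: "Participants who do not meet this criterion will be censored at the time of their last primary outcome evaluation". Death is not mentioned there. Mortality is a separate secondary outcome (4.3.2). Section 10.2.2 alludes in passing to a secondary competing-risk analysis.

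**SAP, objective and headline.** Section 1.2.1 and the opening of 2.1.3.1 keep the walk-test definition. Time runs from randomisation to the "date of first occurrence of major mobility disability assessed by the inability to complete the 400-meter walk test within 15 minutes".

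**SAP, derivation.** Under the heading Derivation of primary endpoint (2.1.3.1), disability is ascertained by a failed test, by a test not done and not adjudicated as free of disability, "or at the date of death if the participants died during the study". Late deaths have their own rule: "or the participant died more than 9 month after the last available visit, then the disability will be considered ascertained" at the last visit plus 183 days, and at randomisation plus 183 days if randomisation was the last visit. A separate closing rule reads: "If no post-baseline visit is done, then participants will be censored at the date of randomization visit V1-T0".

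**SAP, power.** Section 1.3 gives 434 events and 85% power to "detect a 25% reduction in the hazard of major mobility disability over a maximum of 36 months of follow-up".

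**SAP, declared changes.** Section 1.5 says that no amendment changed the protocol's statistical section. Section 1.6, headed "STATISTICAL MODIFICATIONS MADE IN THE STATISTICAL ANALYSIS PLAN", is marked as not applicable.

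**SAP, other analyses.** Section 2.4.4.1 plans a supportive analysis that drops deaths from the event and censors them. Time to death is compared by arm in 2.4.5.3.

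**The concern.** What counts as a primary event differs between the protocol and the SAP's operational rules, and no section records the difference. A reader of the objective, the endpoint definition or a conclusion drawn from them would take the hazard ratio as an effect on walking ability, although some events would be deaths in people with no recorded disability. The hierarchical gate to the whole randomised population (SAP 2.4.4.3) depends on the same test. The planning hazard ratio and event target are attached to disability, so the plan gives no basis for the power of the composite. The derivation also leaves the status of some deaths open.

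**Working it through.** **1. The texts compared.** Take a participant who passes every walk test and then dies.

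- Protocol 10.2.1: does not meet the event definition, so censored at the last evaluation.
- SAP 2.1.3.1: an event, at the date of death or at last visit plus 183 days.
- SAP 2.1.3.2, persistent disability: with no gap over 9 months, censored.
- SAP 2.4.4.1, supportive analysis: censored at the last successful test.

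Only the confirmatory analysis counts this participant as disabled.

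**2. The internal conflict.** Take a participant with no post-baseline visit who dies more than 9 months after randomisation. The late-death rule gives an event at randomisation plus 183 days. The no-visit rule gives censoring at randomisation. Both apply, and no precedence is stated.

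**3. The plan's own figure.** Inputs from protocol 10.1 and 7.4.3.2: hazard ratio 0.75, two-sided 5%, 85% power, 1:1 allocation. Schoenfeld's formula gives D = 4(1.960 + 1.036)² / (ln 0.75)² = 434. The stated figure reproduces for hazard ratio 0.75.

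**4. The composite.** The documents give neither a death rate nor an effect on death, so both are assumed here. Let f be the share of the control-arm composite hazard that is death:

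- composite HR = 0.75(1 − f) + HR_death × f
- power = Φ(½√D × |ln HR| − 1.960)

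Two settings are shown.

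- *Count fixed:* D = 434 composite events in total.
- *N and follow-up fixed:* 600 per arm, uniform 12-month accrual, 24 to 36 months of follow-up, and dropout hazard −ln(0.75)/2 = 0.144 per year. Hazards are exponential. The control disability hazard is solved so that 1,200 participants give 434 disability events; it is 0.254 per year, a 24-month risk of about 40%. The control death hazard is 0.254 × f/(1 − f). Each arm's event probability is λ/(λ+η) × (1 − e^(−(λ+η)u)) averaged over u from 2 to 3 years, where λ is the arm's composite hazard and η the dropout hazard.

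| f | Death HR | Composite HR | Power, count fixed at 434 | Events, N fixed | Power, N fixed |
|---|---|---|---|---|---|
| 5% | 1 | 0.763 | 81% | 454 | 82% |
| 10% | 1 | 0.775 | 76% | 475 | 79% |
| 15% | 1 | 0.788 | 70% | 498 | 76% |
| 20% | 1 | 0.800 | 64% | 523 | 72% |
| 5% | 0.90 | 0.758 | 82% | 453 | 84% |
| 10% | 0.90 | 0.765 | 80% | 473 | 83% |
| 15% | 0.90 | 0.773 | 77% | 495 | 82% |
| 20% | 0.90 | 0.780 | 74% | 518 | 81% |

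With death HR 0.75 the composite HR stays at 0.75 and no power is lost. For comparison, a disability-only analysis with death HR 1, N fixed and deaths censored has power of about 85%, 84%, 83% and 83% across the four shares.

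**5. The supportive curve.** Censoring deaths and plotting one minus Kaplan-Meier overstates disability incidence when death competes. At 3 years, compare 1 − e^(−3a) with a/(a+b) × (1 − e^(−3(a+b))), where a is the disability hazard and b the death hazard per year, both assumed:

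- a = 0.12, b = 0.03: 30.2% against 29.0%
- a = 0.25, b = 0.05: 52.8% against 49.5%

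**The case against.** The best defence is that disability-or-death is a reasonable endpoint in frail people aged 70 and over, and that the SAP does not hide the components. The supportive analysis repeats the stratified log-rank and Cox analysis with deaths censored, and time to death is compared by arm, so a result driven by mortality would be visible. If the intervention has no effect on death, the composite is pulled towards the null, which is conservative. All of this stands. It does not cure the labelling, because the confirmatory test and the gate stay on the composite.

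Several stronger readings are tempting but unsupported.

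- *Every death is an event.* A death after earlier disability adds nothing, and the gap and no-visit rules censor some participants.
- *The protocol explicitly censors deaths.* It reaches them only through a general rule that never names death.
- *The planning hazard ratio is known to exclude deaths.* SAP 1.3 labels the source outcome as walk-test failure, but the SAP uses almost the same label for an endpoint that includes death. The documents do not say how the source trial handled deaths.
- *The 85% is wrong, and power is really 64% to 81%.* Those figures need both a final composite count of only 434 and no effect on death. The extensions in SAP 1.3 are set in months, so deaths may instead add to the events.
- *Disability alone must be primary.* That is a choice on which statisticians differ.

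Deaths contributing to both a composite and a mortality outcome is ordinary. The Kaplan-Meier point touches only a descriptive curve in the supportive analysis; for the composite itself the method is appropriate.

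**Conclusion.** The point holds as a defect of definition and declaration. The primary test is of disability or death, the documents present it as a test of disability, and no modification is recorded. A positive result would be reported as something other than what was tested. The two rules for deaths without a post-baseline visit also contradict each other.

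The power consequence is conditional: none if the intervention reduces death as much as disability, a few points if death HR is 0.90 with N and follow-up fixed, and up to about 13 points below the stated 85% at a 20% death share with no effect on death. The larger shortfall, to 64%, applies only if the final composite count is 434. These figures use the original accrual and follow-up assumptions. SAP 1.3 does not say whether the blinded count of 215 against 270 expected includes deaths, so the documents cannot settle which setting applies.

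**What to change.** - Record the change to the primary event in SAP 1.6.
- Choose one primary endpoint. If the composite stays, name it *mobility disability or death* in 1.2.1, 2.1.3.1 and every conclusion, and restate the power with an explicit death rate and effect on death. Otherwise return to the protocol's disability-only event as primary and make the composite supportive.
- State whether the 434-event target and the blinded 215 against 270 count include deaths.
- Give an order of precedence between the late-death and no-visit rules in 2.1.3.1.
- Tabulate disability-first and death-first events by arm.
- Use Aalen-Johansen curves for the disability-only analysis. The assumed rates above put the overstatement at about 1 to 3 percentage points at 3 years.

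The cost is SAP wording, one table and one curve, and possibly a less favourable stated power. The composite and the deaths-censored analyses are both already planned.
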